#### Analysis

Data will be analysed using IBM SPSS Statistics for Windows (version 19.0). For the key smoking-related outcome variables, intention-to treat analyses will be conducted, together with subgroup analyses based on patterns of intervention uptake. For these analyses, missing data will be classified nonabstinent or as failing to achieve reduction. Odds ratios and associated confidence intervals (CI) will be reported, with the control group as the reference point (odds ratio = 1.00). For the continuous outcome variables (e.g., daily cigarette consumption), planned comparisons between follow-up points, from repeated-measures analyses of variance (ANOVAs), will be used to examine group differences in patterns of change. As a partial control for the number of statistical tests, the threshold for statistical significance will be set at p < 0.01. Among this population, evidence of satisfactory engagement with post-discharge support services and progressive changes in smoking behaviour are also considered highly desirable outcomes. The projected sample sizes should also be sufficient to allow an examination of correlations between selected participant characteristics and aggregate indices of engagement based on the various process measures.

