#### Primary outcome measures

The primary outcomes of this trial relate to changes in participants' smoking behaviour. Smoking behaviour will be assessed at each of the four follow-up surveys (one week, two, four and six months) by: daily cigarette consumption; number and duration of quit attempts; and self-reported abstinence. Daily cigarette consumption and quit attempts are recognised and recommended outcome measures which are frequently used in this population [62,63]. When abstinence is reported, it will be verified by exhaled carbon monoxide (CO) levels using a MICRO+ Smokerlyzer, with a cut-off of < 10 ppm [42,63]. CO validation tests will be arranged during the follow-up surveys and will be conducted by a project officer within 3 days of the survey (with smoking status attained again at that time), in a public location convenient to the participant (eg. library) or, if not viable, conducted as a home visit following the institutional safety guidelines.

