### Sample size and detectable difference

A total of 200 participants (approximately 100 per group) will be recruited to the study (an estimated 70 per group at 6 month follow-up, assuming a 70% follow-up rate). This number is sufficient to conduct intention to treat analyses to examine intervention effectiveness (with 80% power and .01 level significance tests) in terms of differences on the continuous outcome measures (e.g., quit attempts, daily cigarette consumption, nicotine dependence) of the order of 0.51 standardised (effect-size) units, and 4.8 fold increases in point prevalence abstinence (e.g., treatment group, 24% abstinent, vs. comparison group, 5% abstinent). A previous, similar sized multimodal intervention study conducted among a mental health patient population demonstrated statistically significant differences (20% effect size or larger) between groups on continuous outcomes including reduction in daily cigarette consumption and nicotine dependence levels, but not for abstinence [21]. Due to the unique methodology and intensity of intervention employed in the current trial, it is uncertain whether this trial will have sufficient power to detect statistically significant differences in abstinence between the two conditions, however significant differences in other outcomes are achievable. It could be argued, based on the novel design of this trial, larger effect sizes may be achieved, but this remains speculative.

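### Daily cigarette consumption appears to be analysed both as a binary reduction and as a continuous measure, and the plan does not say which analysis decides

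*Protocol article*

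**What the plan says.** All four places are in the Protocol article.

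- **Primary outcome measures** lists "daily cigarette consumption; number and duration of quit attempts; and self-reported abstinence". It lists no responder or reduction outcome.
- **Sample size and detectable difference** gives detectable differences of two kinds, "with 80% power and .01 level significance tests": 0.51 SD for continuous measures, with daily cigarette consumption among the examples, and 24% versus 5% for abstinence. It gives none for a binary reduction. When it describes an earlier trial, it treats reduction in daily consumption as a continuous outcome.
- **Analysis**, on the intention-to-treat analyses of the key smoking variables, first says "For these analyses, missing data will be classified nonabstinent or as failing to achieve reduction". It continues: "Odds ratios and associated confidence intervals (CI) will be reported, with the control group as the reference point (odds ratio = 1.00". It then says: "For the continuous outcome variables (e.g., daily cigarette consumption), planned comparisons between follow-up points, from repeated-measures analyses of variance (ANOVAs), will be used". The stated purpose is to compare how the two arms change over time.
- **Analysis**, on multiplicity: "As a partial control for the number of statistical tests, the threshold for statistical significance will be set at p < 0.01".

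**The concern.** A rule that classifies a missing value as a failure to reduce makes sense for a yes/no outcome, and the odds ratios that follow point the same way. Read naturally, one primary measure then has a binary analysis and a continuous one, and no text ranks them.

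The two forms differ in more than scale:

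- The binary form keeps all 200 participants, because missing counts as failure.
- Missing-as-failure cannot be applied to a mean. The ANOVA may therefore rest on those followed up, about 70 per group at six months, and the article gives no separate missing-data rule for it.

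If one analysis crosses 0.01 and the other does not, the text lets either stand as the consumption result. The reader could not tell which one the trial had committed to.

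**Working it through.** **1. The plan's own figure.** The smallest detectable standardised difference is (z for 0.995 + z for 0.80) × √(2/n), two-sided at 0.01.

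- n = 70 per group: 3.417 × √(2/70) = 0.578 SD.
- n = 100 per group: 3.417 × √(2/100) = 0.483 SD.
- 0.51 SD needs 90 per group. Power for it is 67% at 70 per group and 85% at 100.

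So 0.51 SD does not reproduce at 70 per group. That is a separate matter. Here 0.51 SD serves only as the plan's own size of effect. No figure exists to reproduce for a binary reduction.

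**2. Error from two tests of one measure at one time point, each at 0.01.**

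- If independent: 1 − (1 − 0.01)² = 0.0199.
- Upper bound whatever the correlation: 0.01 + 0.01 = 0.02.
- Simulated: about 1.6-2.1%. Values just above 2% are simulation noise around the bound.

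**3. How often the two forms disagree.** The document gives no SD and no reduction rates, so every distributional input is an assumption. Both models use 100 per arm, 30% missing at random, and two-sided 0.01. The binary test counts missing as failure, and the continuous test uses those followed up.

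*Model A.* Mean 22 and SD 12 cigarettes per day, rounded and floored at zero; baseline/follow-up correlation 0.3-0.7; control-arm fall of 0 or 0.5 SD; true effect 0.51 SD.

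| Test | Power |
|---|---|
| Baseline-adjusted mean consumption | 67-93% |
| Mean change from baseline | 38-88% |
| Odds-ratio form, any drop counts, missing = failure | 12-48% |

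Mean change and any-drop differ on significance in about 32-64% of trials. Allowing a 50% cut as well lowers the bottom of the range to about 27%.

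*Model B.* Baseline mean 20 and SD 9; follow-up equal to 0.8 × baseline plus residual SD 8, floored at zero; true shift 0.6 × 8 = 4.8 cigarettes. The SD of change is √(0.2² × 81 + 64) = 8.2, and 4.8/8.2 = 0.585, so this effect is somewhat larger than 0.51 SD.

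| Test | Power | Differs from continuous test |
|---|---|---|
| Mean change | 74% | – |
| Any reduction | 19% | 58% |
| At least 25% | 42% | 39% |
| At least 50% | 43% | 40% |
| At least 75% | 27% | 54% |

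In both models disagreement means that one test is significant and the other is not. The change test is a single-time-point stand-in for the planned repeated-measures comparisons.

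**The case against.** **There may be no second test.** The article never declares a binary reduction endpoint, and its sample size section treats reduction as continuous. The missing-data sentence could mean that a missing consumption value is taken as no change from baseline, with odds ratios for abstinence only. This reading is possible and cannot be excluded. The wording about classifying and failing to achieve, directly before odds ratios, makes the two-form reading the more natural one. It remains an inference, and the text should be made to settle it.

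**A reader might infer that the cut-off is missing, or will be picked after the data are seen.** The documents do not support that. This is a condensed article, and a responder threshold is commonly left to a full protocol or analysis plan, which is not shown. A threshold alone would still not say which form decides.

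**A reader might infer serious error inflation.** The plan adopts p < 0.01 expressly as partial control for multiple tests, and two tests stay at or below 2%. Error rates of 2.4-4.3% arise only if two to four cut-offs are tried together, which the article does not propose. The larger multiplicity lies in several unranked primary measures at four time points, which is a different question.

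**A reader might infer opposite answers.** The simulations show discordant significance, as expected from tests of unequal power. They do not show effects in opposite directions.

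**The low power may reflect the worst definition.** This is partly right. Any-drop is the least favourable cut overall, and a 25% or 50% cut does better, though in Model B it still falls well below the continuous test. Nor does the plan discard the continuous information, since it keeps the ANOVA and was sized on continuous measures.

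**Conclusion.** The point holds as one of unclear priority. The Analysis section appears to give a primary measure two analyses and names neither as deciding; the binary one is neither a listed outcome nor covered by the sample size. The effect on error is small: at most about 2% per time point against a nominal 1%. The effect on interpretation is larger: with a true effect of the size the plan assumes, the two forms would differ on significance in roughly 27-64% of trials, and the binary form with missing as failure is usually much the weaker. These percentages rest on assumed means, SDs, correlations and reduction rates, on data missing at random, and on a stand-in for the planned ANOVA. They show the scale of the problem and do not predict this trial's result.

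**What to change.** Amend the Analysis section as follows.

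1. Make one analysis the deciding test of consumption: cigarettes per day on the original scale, adjusted for the baseline value. In Model A this had 67-93% power, against 38-88% for mean change.
2. State how missing consumption values are handled in that analysis, because missing-as-failure fits only binary outcomes. Without this step, narrowing the existing sentence would leave consumption with no rule at all.
3. Apply the odds-ratio and missing-as-failure sentences to abstinence.
4. If a binary reduction is kept, use one cut-off fixed before unblinding and label it supportive.

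The cost is wording only, with no new data. The small downside is that a significant reduction odds ratio alone could no longer be claimed as a primary result. Which of the four time points decides is a separate question that this change does not settle.

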### Intervention condition

In addition to hospital smoking care, the participants randomised to the intervention condition will be provided with a 'base' intervention component, comprising a brief motivational interview and smoking cessation self-help material in the inpatient setting. Participants will also be offered the following 'additional' components of the intervention, to occur post discharge: up to 12 weeks of ongoing NRT; a proactive Quitline referral; and a referral to community smoking cessation support groups. Upon discharge, participants will receive an initial two week supply of NRT, and their participation in the study will be recorded on the hospital discharge summary and sent to relevant treating practitioners in the community. Participants will additionally receive supportive phone contact at three days, and one week post hospitalisation, and the delivery of the elected intervention components will commence. Subsequently, participants electing any of the 'additional' intervention components will concurrently receive up to 16 weeks of further fortnightly telephone support.

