### Data collection and measures

#### Baseline

The baseline survey will be administered as a face to face interview by project officers, within the inpatient setting prior to the allocation of treatment condition, and will be of up to 1 hour duration for both groups.

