#### Follow-up data collection

Follow-up data will be collected for both groups via blind telephone interview at one week, two months, four months and six months post discharge. To enable subsequent assessment of the effectiveness of the blinding, interviewers will be asked at the completion of the interview to indicate the treatment condition to which they believe the participant was allocated. If any participant experiences an acute phase of their psychiatric disorder during any of the follow-up phone interviews, they will be encouraged to contact their GP, psychologist or community mental health team. Participation will continue as normal unless the participant expresses severe psychological distress and/or they no longer wish to participate in the trial. To minimise attrition, notices will be mailed, one week prior the due date, to remind participants of each upcoming follow-up call [61]. The protocol for follow-up calls will comprise up to four weeks of call attempts, with at least 10 attempts made within the first seven days of the due date, and regular attempts thereafter. At the completion of the six month follow-up interview, a letter will be mailed to participants, notifying them that their participation is complete and thanking them for their contribution to the study.

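### The named test for continuous outcomes contrasts follow-up points that all fall after treatment starts, so it removes whatever benefit is already present at one week

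*Protocol article*

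**What the plan says.** Daily cigarette consumption is one of the primary outcomes (Primary outcome measures). For the continuous outcomes, with daily consumption as the example, the Analysis section states that "planned comparisons between follow-up points, from repeated-measures analyses of variance (ANOVAs), will be used to examine group differences in patterns of change". It adds that "the threshold for statistical significance will be set at p < 0.01".

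The follow-up points are fixed elsewhere: "Follow-up data will be collected for both groups via blind telephone interview at one week, two months, four months and six months post discharge". Baseline is a separate survey, done "within the inpatient setting prior to the allocation of treatment condition".

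Treatment starts before the first follow-up. The motivational interview takes place in hospital. On NRT, the Intervention condition section says "Upon discharge, participants will receive an initial two week supply of NRT". A support call follows at three days, and another at one week.

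The sample-size section describes the detectable effect on continuous outcomes as a difference "of the order of 0.51 standardised (effect-size) units", "with 80% power and .01 level significance tests".

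**The concern.** The study aim is to reduce smoking and encourage quitting after discharge, and the sample size rests on a difference between groups. A group difference in a contrast between two follow-up visits answers another question: whether the arms moved further apart, or closer together, between those visits. The one-week value is already an outcome under treatment, so subtracting it subtracts treatment effect.

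Three patterns show what is at stake:
- A benefit reached by week one and then held gives an expected contrast of zero.
- A benefit partly present at week one is credited only with its later growth.
- A benefit that wanes gives a contrast toward control, even if the intervention arm smokes less at every visit. This pattern is plausible: NRT is offered for up to 12 weeks and telephone support for up to 16, so the six-month visit comes after both have ended.

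A trial with a real reduction in consumption could therefore report no significant result on the one test that the section names for that outcome.

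**Working it through.** **Inputs from the protocol article.** Difference 0.51 SD, significance level 0.01, about 70 per group at six months and 100 per group recruited (Sample size and detectable difference); four follow-up visits (Follow-up data collection).

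**Assumptions.** Two-sided tests, since the article does not state sidedness. Equal correlation ρ between all visits, taken as 0.3, 0.5 and 0.7, because the article gives none. SD is set to 1.

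**The plan's own figure.** Detectable difference = (2.576 + 0.842) × √(2/n).
- n = 70: 3.418 × 0.169 = 0.58 SD. Power for 0.51 SD is 67%.
- n = 100: 3.418 × 0.141 = 0.48 SD. Power for 0.51 SD is 85%.

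The stated 0.51 SD with 80% power is not reproduced at either size; it needs 90 per group. That is a separate matter, and nothing below depends on it. What matters here is that the quantity is a between-group difference.

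**Formula for the named contrast.** For six months minus one week, with arm differences d6 and d1:
- expected value = d6 − d1
- standard error = √[2(1 − ρ)] × √(2/n)
- power ≈ Φ(z − 2.576) + Φ(−z − 2.576), where z = |expected value| / standard error

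**Constant benefit.** d6 − d1 = 0.51 − 0.51 = 0, so z = 0 and rejection is 1.0% at any ρ and any n. Simulation (20,000 trials, 70 per group, ρ = 0.5) gave 1.1% for six months minus one week, 1.1% for the linear trend over follow-ups and 1.0% for the omnibus group-by-time test over the four follow-ups.

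**Half the benefit present at one week.** d6 − d1 = 0.51 − 0.255 = 0.255, n = 70:
- ρ = 0.3: SE = 1.183 × 0.169 = 0.200, z = 1.27, power 10%
- ρ = 0.5: SE = 1.000 × 0.169 = 0.169, z = 1.51, power 14%
- ρ = 0.7: SE = 0.775 × 0.169 = 0.131, z = 1.95, power 27%

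With 100 per group the range is 15% to 40%.

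**Waning benefit, 0.7 SD at one week to 0.4 SD at six months.** d6 − d1 = −0.3. At ρ = 0.5 and n = 70, z = 0.3/0.169 = 1.77, so rejection is about 20%, and the contrast points toward control.

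**Summary, 70 per group**

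| Test | Constant 0.51 SD (ρ 0.3 / 0.5 / 0.7) | Half at one week | None at one week |
|---|---|---|---|
| Six months minus one week | 1% / 1% / 1% | 10% / 14% / 27% | 49% / 67% / 91% |
| Six months minus baseline | 49% / 67% / 91% | 49% / 67% / 91% | 49% / 67% / 91% |
| Six-month difference, unadjusted | 67% | 67% | 67% |

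The named contrast matches a contrast from baseline only if no effect is present at one week.

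**Value of adjusting for baseline.** For the six-month comparison at ρ = 0.5 and n = 70:
- change score: SE = 0.169, z = 0.51/0.169 = 3.02, power 67% (66% in 4,000 simulated trials)
- baseline-adjusted: SE = 0.169 × √(1 − 0.25) = 0.146, z = 0.51/0.146 = 3.48, power 82% (80% in simulation)

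In the waning case, the baseline-adjusted six-month comparison had 56% power in simulation.

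**The case against.** The strongest reply is that one condensed sentence is being read literally. Its stated purpose concerns patterns of change, the primary outcomes are described as changes in smoking behaviour, and a reduction outcome needs a pre-treatment reference. All of this fits a repeated-measures ANOVA with baseline as one level. On that reading the 1% result disappears, and only the lower precision of change scores remains. This reading may be what was meant. But the sentence names follow-up points, and the article consistently uses that term for the four post-discharge surveys.

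A reader might infer that the plan cannot detect a sustained benefit at all. The documents do not support that, for three reasons:
- A repeated-measures ANOVA also yields a group main effect. Under a constant 0.51 SD benefit, the mean over four follow-ups would have 89% power at ρ = 0.5 with 70 per group. The section does not name it as the test, but does not exclude it.
- The same section plans intention-to-treat odds ratios, with missing data counted as non-abstinent or as no reduction. Those comparisons do not cancel an early effect, though they do not replace the continuous test.
- Total loss requires the whole effect to be present by week one. Much of the package comes later, and the one-week support call need not precede the one-week survey.

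A contrast that shows waning also describes the time course correctly. The difficulty arises only when it serves as the efficacy test. Nor do the documents support extending the point to how quit attempts are counted, because they state no recall window.

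**Conclusion.** The point holds for the text as written. The only test named for continuous outcomes removes any effect already present at one week, and it matches neither the aim nor the between-group difference in the sample-size section. The loss ranges from complete (1% rejection for an effect constant from week one), through 10% to 27% power when half the effect is present by then, to none relative to a contrast from baseline when no effect is present at one week. The zero expectation under a constant effect needs no assumption about correlation. The intermediate powers rest on assumed correlations of 0.3 to 0.7, equal correlation across visits and two-sided testing.

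The size of the problem in practice depends on whether baseline was meant to be in the contrasts and on how much benefit appears in the first week. The article settles neither. This is therefore a misdirected or misworded efficacy test that needs correcting, not proof that the trial would miss a benefit.

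**What to change.** State the efficacy test for daily cigarette consumption as the between-arm difference at a named follow-up, for example six months, adjusted for the baseline value and the diagnosis stratum. Take it from a repeated-measures or mixed model that also reports the earlier visits. Keep contrasts between follow-up points as a description of the time course.

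If contrasts from baseline were intended, say so explicitly. Baseline adjustment would still be worth adopting, since it is more precise than change scores (about 80% against 66% power at an assumed correlation of 0.5).

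The cost is a small change of wording and analysis, with the same data and the same SPSS software. It should be settled before outcomes are compared by arm.

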## Discussion

The research literature indicates no previously published randomised control trials internationally to evaluate the effectiveness of an integrated smoking cessation intervention for mental health inpatients, linking inpatient smoking care with community cessation supports. This multimodal, integrated intervention design has been developed to maximise the likelihood of positive smoking outcomes for mental health patients, and aims to demonstrate the feasibility, acceptability and potential efficacy of linking inpatient smoking care to community cessation support. The study demonstrates many strengths. Firstly, most smoking cessation interventions for persons with a mental illness to date have focused on specific diagnostic groups, particularly, samples with schizophrenia or schizoaffective disorders [33]; and have further required patients to express a willingness or desire to quit for participation [19]. The methodology employed in this trial is particularly unique. No previous studies have directly examined the effect of linking inpatient smoking care to community cessation support for mental health patients, and only very few have been conducted in the general hospital setting [67,68]. In the current trial, we aim to employ a 'real life' approach, working within existing mental health services, systematically approaching patients and determining smoking status, and offering the project regardless of diagnosis or motivation to quit. By offering participation to a heterogeneous sample of diagnostic groups and motivation levels, this trial may demonstrate the effectiveness of providing integrated smoking cessation treatment to mental health inpatients in a systematic manner that may be incorporated into existing mental health settings.

